### Sample size estimation

To date, no studies have been done to determine whether HMB-enriched nutritional supplements are effective and safe for improving muscle mass and muscle function in obese adults during weight loss. To determine the sample size, we examined similar studies on HMB and referred to the study by Peng and Cheng that evaluated the effectiveness of HMB for improving SMM and quality in prefrail older adults.^12^ Using a 0.05 significance level, 80% statistical power and 25% attrition rate, a sample size of 70 has been assumed using an assumed effective size of 0.93. Moreover, to achieve a gender-balanced distribution within and between groups, a random stratification method including 36 samples per gender is proposed, adding up to 72 samples in total.

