### Statistical analysis plan

The statistical analysis will be performed by an independent statistical expert blinded to the group allocation. SPSS V.26.0 (IBM) and R V.4.0.3 (R Foundation for Statistical Computing, Vienna, Austria) will be used for statistical analysis.

Each group will be summarised in terms of demographic characteristics and baseline variables. For comparisons of continuous variables, two-sample t-tests or Mann-Whitney U tests will be used, whereas for categorical variables, the χ^2^ test or Fisher’s exact test will be used.

As aforementioned, the primary outcome will be in SMM from the beginning to the end of the 12-week intervention. The independent two-sample t-test or Mann-Whitney U test will be used based on the distributional normality. We will make adjustments based on the covariates if there are significant demographic differences between the groups or if baseline variables differ significantly. In the primary analysis, the full analysis set (FAS) will be the main data set. Participants initially assigned to either group will be included in the FAS. However, our analysis will not use the data of ineligible participants (ie, those who are wrongly enrolled because of measurement or human error), subjects who received less than 75% of the planned intervention or subjects without the primary outcome measurement. For sensitivity analysis, we will use a protocol-specific set to compare with the results from the FAS. A per-protocol analysis will include participants who achieved the completion of the study without major deviations from protocol, who provided the primary outcome and who received at least 75% of the planned intervention. The rate of protocol compliance in each group will be calculated. A significance level of two-sided p<0.05 will be used. If needed, the multiple imputation method will be adopted for missing data.

We will use the same methods for analysing secondary outcomes as we did for analysing the primary outcome. A paired t-test or Wilcoxon signed-rank test will be used to assess the changes in outcome measures within groups before and after the intervention. To validate trend differences per visit, we will use repeated measures analysis of variance with post hoc tests.

Moreover, subgroup analysis will be done to identify whether gender or Asian Working Group on Sarcopenia-defined sarcopenia^30^ at baseline would affect the clinical response to HMB-enriched nutritional supplements.

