## Discussion

This study will be a randomised, double-blind, parallel-group, placebo-controlled trial aiming to explore the effectiveness and safety of HMB-enriched nutritional supplements for improving muscle mass and muscle strength in obese adults during the weight loss process using calorie restriction. It will determine the feasibility of future large-scale clinical trials on HMB-based interventions for improving body composition (especially muscle health) in obese adults when performing weight loss plans.

The effectiveness of HMB for improving muscle mass and muscle strength has been well studied in athletes, healthy adults, older adults and patients with cancer.^33^ However, we found only two clinical trials addressing the effectiveness of HMB on muscle health in obese adults.^34 35^ In 2019, an RCT conducted in Iran demonstrated that supplementing with HMB for 6 weeks reduced weight, waist and abdominal circumference, and even increased strength without resistance training, and without affecting lean mass, in sedentary and overweight women.^34^ Most recently, Rondanelli *et al*^35^ conducted an RCT in obese or overweight Italian menopausal women. Using an oral nutrition supplement containing arginine, glutamine and HMB for 4 weeks, they observed that visceral adipose tissue and BFM were statistically significantly reduced, whereas fat-free mass (mainly muscle mass) remained the same.

Our trial has some strengths. First, it will be the first to evaluate the effectiveness of HMB-enriched nutritional supplements for improving muscle health in Chinese obese adults. Second, we will use a double-blinded design to minimise bias due to demand characteristics, the placebo effect and measurement bias. Last, we will focus on muscle mass and fat mass and muscle function (ie, HGS and physical performance).

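### The stated sample size of 70 does not follow from the stated inputs, which give 54; at least one input is misreported, and the error is on the safe side

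*Protocol article*

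**What the plan says.** Under Sample size estimation, the protocol article gives the inputs and the result together: "Using a 0.05 significance level, 80% statistical power and 25% attrition rate, a sample size of 70 has been assumed", then "using an assumed effective size of 0.93". The effect size comes from a study of HMB in prefrail older adults. The paragraph gives no mean difference, no standard deviation, no test and no sidedness. It then raises 70 to 72 so that 36 participants of each gender can be enrolled.

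Two other sections supply what is missing. Study design gives 1:1 allocation. The Statistical analysis plan section compares the primary outcome by independent two-sample t-test or Mann-Whitney U test, depending on normality, and states: "A significance level of two-sided p<0.05 will be used".

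**The concern.** The protocol prints a complete set of inputs and a result that does not follow from them. This is not detail that an article may leave to a longer document, because no further document can make the printed sentence true.

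The paragraph is the only justification given for the number of people enrolled. A reader will take 80% power at 0.93 SD as the property of the design. If the result is null, the same reader will use that statement to judge which effects the trial could have detected. As printed, the sentence cannot be right on power, effect size, attrition and total all at once.

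**Working it through.** **Inputs.** Significance level 0.05, power 80%, effect size d = 0.93 and attrition 25% are from Sample size estimation. Two-sided testing and the t-test or Mann-Whitney U test are from Statistical analysis plan. Allocation 1:1 is from Study design.

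**Step 1: try to reproduce 70.** The normal approximation is n per arm = 2(z₀.₉₇₅ + z₀.₈₀)²/d² = 2(1.960 + 0.842)²/0.93² = 18.15, so 19. The exact calculation with the noncentral t distribution gives 19.16, so 20 per arm and 40 evaluable. Allowing for attrition, 40/(1 − 0.25) = 53.3, so 54. The stated 70 is 16 more, or about 30% higher (70/54 = 1.30).

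**Step 2: try other conventions, keeping 80% power, alpha 0.05 and d = 0.93.**

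| Convention | Total with attrition |
|---|---|
| Two-sided t-test | 54 |
| Normal approximation, each arm rounded up | 52 |
| Mann-Whitney, usual factor π/3 (20.06, so 21 per arm) | 56 |
| Mann-Whitney, worst-case efficiency 0.864 (23 per arm) | 62 |
| Multiplying by 1.25 instead of dividing by 0.75 (all two-sided variants) | 48 to 58 |
| One-sided tests, dividing by 0.75 | 40 to 48 |

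None reaches 70. The gender-balance step explains only the move from 70 to 72.

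**Step 3: find what would give 70.**

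- 90% power at d = 0.93: 25.30, so 26 per arm and 52 evaluable; 52/0.75 = 69.3, so 70.
- 80% power at d = 0.80: 25.52, so 26 per arm and 52 evaluable; again 70.
- 80% power at d = 0.93 with 40 evaluable out of 70: attrition would have to be 1 − 40/70 = 43%, against the stated 25%.

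The first two each change one input to a round value and fit exactly. Nothing in the protocol favours one over the other.

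**Step 4: what the design delivers.** With 72 randomised and 25% lost equally from both arms, 72 × 0.75 = 54 are evaluable, or 27 per arm (two-sided 0.05).

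| Test | Power at 0.93 SD | Effect detectable with 80% power |
|---|---|---|
| t-test | 91.8% | 0.777 SD |
| Mann-Whitney (27 × 3/π = 25.8 effective per arm) | 90.6% | 0.796 SD |

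**The case against.** The strongest reply is that nobody is harmed. If 0.93 is the planned effect, 72 is well above the 54 required and power is about 92%, so the promised 80% is more than met. Enrolment, allocation and the primary analysis all stay the same. This stands. It makes the point a reporting correction and not a fault in the design, but it does not make the printed calculation right.

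A second reply is that the mismatch does not show which figure is wrong. This also stands. A reader might infer that 80% is a misprint for 90%, since 90% fits exactly. An effect size of 0.80 fits just as exactly, and the protocol does not settle it. For the same reason it would be wrong to say that both the power and the effect size are misstated; those are alternative readings of one discrepancy.

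A reader might also go further and argue that 0.93 is too optimistic, because the Discussion cites two trials in overweight or obese people. One did not affect lean mass, and of the other it says "whereas fat-free mass (mainly muscle mass) remained the same". The documents do not support that step. The Discussion gives no between-group difference and no standard deviation for either trial. They lasted 6 and 4 weeks, against 12 here, and one enrolled menopausal women, whom this trial excludes. The Discussion does not say that either used calorie restriction. In a trial about preserving muscle during calorie restriction, stable fat-free mass on the supplement is compatible with a benefit if controls lose muscle. Sample size estimation also says openly that no study in the target population was available. A warning about low power for small effects would therefore be optional commentary; the protocol already calls its sample relatively small.

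**Conclusion.** The sample size statement is wrong as written and should be corrected. The stated inputs give 54 (56 with the usual Mann-Whitney allowance), not 70, and no standard variant at 80% power and alpha 0.05 closes the gap. At least one printed input differs from the one used, and the protocol does not show which.

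The error is conservative. A reader might take the mismatch to mean that the trial is underpowered, but under its own stated assumptions it is larger than it needs to be.

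The conclusion rests on two-sided testing (stated for the analysis and not in the sample size paragraph), 1:1 allocation, and 0.93 being a standardised mean difference between arms. The delivered power also assumes that 25% attrition falls equally on both arms.

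**What to change.** Keep 72. In Sample size estimation, restate the power and effect size actually used, correcting whichever was misprinted, and name the test and its sidedness. The authors need to consult their own calculation for this; the value should not be guessed from the fit.

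Then add a sentence that holds whichever input was wrong: 72 randomised, 54 evaluable after 25% attrition, gives about 92% power for a standardised difference of 0.93, or 80% power for about 0.78, by two-sided t-test at 0.05. If the Mann-Whitney test is used, the figures are about 91% and 0.80.

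The cost is a few sentences, with no change to enrolment, allocation or analysis.

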### Statistical analysis plan

The statistical analysis will be performed by an independent statistical expert blinded to the group allocation. SPSS V.26.0 (IBM) and R V.4.0.3 (R Foundation for Statistical Computing, Vienna, Austria) will be used for statistical analysis.

Each group will be summarised in terms of demographic characteristics and baseline variables. For comparisons of continuous variables, two-sample t-tests or Mann-Whitney U tests will be used, whereas for categorical variables, the χ^2^ test or Fisher’s exact test will be used.

As aforementioned, the primary outcome will be in SMM from the beginning to the end of the 12-week intervention. The independent two-sample t-test or Mann-Whitney U test will be used based on the distributional normality. We will make adjustments based on the covariates if there are significant demographic differences between the groups or if baseline variables differ significantly. In the primary analysis, the full analysis set (FAS) will be the main data set. Participants initially assigned to either group will be included in the FAS. However, our analysis will not use the data of ineligible participants (ie, those who are wrongly enrolled because of measurement or human error), subjects who received less than 75% of the planned intervention or subjects without the primary outcome measurement. For sensitivity analysis, we will use a protocol-specific set to compare with the results from the FAS. A per-protocol analysis will include participants who achieved the completion of the study without major deviations from protocol, who provided the primary outcome and who received at least 75% of the planned intervention. The rate of protocol compliance in each group will be calculated. A significance level of two-sided p<0.05 will be used. If needed, the multiple imputation method will be adopted for missing data.

We will use the same methods for analysing secondary outcomes as we did for analysing the primary outcome. A paired t-test or Wilcoxon signed-rank test will be used to assess the changes in outcome measures within groups before and after the intervention. To validate trend differences per visit, we will use repeated measures analysis of variance with post hoc tests.

Moreover, subgroup analysis will be done to identify whether gender or Asian Working Group on Sarcopenia-defined sarcopenia^30^ at baseline would affect the clinical response to HMB-enriched nutritional supplements.

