## Methods and analysis

### Study design

We designed a single-centre, randomised, parallel-group, double-blind, placebo-controlled trial. We plan to recruit 72 Chinese obese adults who intend to perform weight loss via calorie restriction. The participants will be randomly assigned to either the intervention group or the control group at a 1:1 ratio and will receive HMB-enriched nutritional supplements or placebo, respectively, for 12 weeks. The flow chart of this trial is presented in figure 1 while the overall schedule of this trial is shown in table 1.

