### Randomisation and allocation concealment

We will use the stratified block randomisation method to perform randomisation. A random number sequence will be automatically generated by R V.4.0.3 (R Foundation for Statistical Computing, Vienna, Austria) before the inclusion of the first participants. Gender is first used as a stratification factor, and 36 cases of each gender will be included, and then block group randomisation will be performed for each gender, with block group lengths set to 2–8 and randomly selected by the computer.

To perform allocation concealment, we will seal the randomisation list in sequentially numbered opaque envelopes. The envelopes will be opened sequentially at the beginning of the intervention in the order of entry, and the grouping of participants will be determined according to the allocation scheme inside the envelope.

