#### Primary outcome

The mean change in whole-body skeletal muscle mass (SMM) from the beginning to the end of the 12-week intervention will be measured for all participants. The whole-body lean body mass will be measured by trained research staff using a bioimpedance analysis device (BIA; InBody 770; Biospace, Seoul, Korea). The participants will be guided through the BIA test. They will be asked to stand upright at least 5 min before testing, then to step on the footplate barefoot with their heels on the rear sole electrodes and their hand holding the hand electrode. Their arms should be straight and should not touch the side of the body during the test.

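### Gender stratifies the randomisation but can enter the primary analysis only through a baseline significance test that stratification makes very unlikely to fire; pre-specifying it is a free gain in precision

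*Protocol article*

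**What the plan says.** **Design.** Under Randomisation and allocation concealment: "Gender is first used as a stratification factor, and 36 cases of each gender will be included", with blocks of varying length inside each gender. Sample size estimation repeats this: "a random stratification method including 36 samples per gender is proposed, adding up to 72 samples in total". Allocation is 1:1 (Study design).

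**Outcome.** Under Primary outcome: "The mean change in whole-body skeletal muscle mass (SMM) from the beginning to the end of the 12-week intervention".

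**Analysis.** Under Statistical analysis plan: "The independent two-sample t-test or Mann-Whitney U test will be used based on the distributional normality". The next sentence adds covariate adjustment, but only when demographic or baseline variables turn out to differ significantly between the arms. The same methods are carried over to the secondary outcomes. Gender is named in the analysis only as a subgroup factor. The Discussion adds adjustment for physical activity and energy intake. No section puts gender or baseline SMM into the primary comparison unconditionally.

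**The concern.** Stratifying on gender removes chance gender imbalance from the treatment contrast, so any gender effect on SMM change no longer contributes to the sampling variation of the estimated difference. A two-sample t-test does not know this and leaves the between-gender variance in its error term. If men and women change by different amounts in kilograms, the standard error is overstated, the interval is wider than the design warrants, and power is lost. The Mann-Whitney test shares the problem.

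The conditional rule does not repair this. It picks covariates by observed imbalance, whereas the value of a covariate lies in how well it predicts the outcome. Gender is the variable that the design forces into balance, so it is the one the rule is least likely to select. The rule also lets the data choose the primary model.

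**Working it through.** **The plan's own figure.** Sample size estimation states: "Using a 0.05 significance level, 80% statistical power and 25% attrition rate, a sample size of 70 has been assumed". The effect size behind this figure is 0.93. Read as a standardised difference with two-sided alpha 0.05, n per arm = 2(1.960 + 0.842)²/0.93² = 18.2, so 19, or 20 with the t distribution. That is 40 evaluable and 40/0.75 = 53.3, so 54 enrolled. The stated 70 is not reproduced. It matches 90% power (26 per arm; 52/0.75 = 69.3, so 70). This is a separate matter. What counts here is that 72 × 0.75 = 54 evaluable, 27 per arm, gives an unadjusted power of 91.8% at 0.93 when gender has no effect on change.

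**Can the trigger bring gender in?** Assume even block lengths up to 8. The worst split within a gender of 36 is an unfinished last block with four consecutive allocations to one arm, 20:16. If both genders reach this in opposite directions, the arms hold 20 men and 16 women against 16 men and 20 women. Then χ² = 72(20×20 − 16×16)²/36⁴ = 0.89 on 1 df, well below 3.84. So gender cannot differ significantly among those randomised; only lopsided exclusions afterwards could change that. In a simulation of baseline SMM (26 per arm, genders assumed 2.6 within-gender SD apart), the trigger fired in under 0.3% of runs.

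**What omission of gender costs.** Let D be the gender difference in mean SMM change, in within-gender SD. The documents do not give D, so a range is shown.
- The t-test's error variance is about 1 + D²/4, where the true value is 1, so its standard error is too large by k = √(1 + D²/4).
- Gender's share of the variance in change is (D²/4)/(1 + D²/4).
- True standard error at 27 per arm: √(2/27) = 0.272. Critical value: 2.007 (52 df).
- Approximate type I error: P(|t| > 2.007k). Approximate power: Φ(d/0.272 − 2.007k).

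| D | gender's share of variance | k | type I error | power, d = 0.93 | power, d = 0.60 |
|---|---|---|---|---|---|
| 0 | 0% | 1.000 | 5.0% | 92% | 58% |
| 0.5 | 6% | 1.031 | 4.4% | 91% | 55% |
| 1.0 | 20% | 1.118 | 2.9% | 88% | 48% |
| 1.5 | 36% | 1.250 | 1.5% | 82% | 38% |

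With gender in the model, type I error stays near 5% and power near 92% and 58% in every row.

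**Simulation.** With 54 evaluable, from exact balance within gender to random dropout from 72, type I error is about 5.0 / 4.2–4.5 / 2.9–3.6 / 1.4–2.1%. Power is about 92 / 91 / 87 / 80% at 0.93 and 58 / 55 / 49 / 38% at 0.60. Repeat runs differ by a few tenths of a point in type I error and by a point or two in power.

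**Baseline SMM.** Assume equal variances σ² at baseline and week 12, with correlation r. A change score has variance 2σ²(1 − r) and ANCOVA has σ²(1 − r²), so the ratio is (1 + r)/2. That is 0.90, 0.95 and 0.975 at r = 0.80, 0.90 and 0.95 (r is not in the documents). At r = 0.90 the standard error falls by about 2.5%.

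**The case against.** **The plan is not simply unadjusted.** It has a conditional rule, and the Discussion promises adjustment for activity and intake. This stands as a description. It does not answer the point, because the rule will practically never select gender and the Discussion names neither gender nor baseline SMM.

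**Baseline SMM is not ignored.** This stands. The outcome is a change from baseline, so baseline is already subtracted, and adding it as a covariate gains only a little.

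**The loss depends on an unstated quantity.** This also stands. That men carry more muscle in kilograms does not show how far their 12-week changes differ from women's. At D = 0 nothing is lost, and at 0.5 SD very little. Material loss begins near 1.0 SD, where gender would explain a fifth of the variance in change.

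**Power is ample at the protocol's own effect size.** At 0.93 the t-test still has about 80% power even at D = 1.5. If 0.93 is scaled by the total SD and not the within-gender SD, unadjusted power stays at about 92% or above, and adjustment for gender and baseline together adds about 1 to 6 points for an explained variance of 0.05 to 0.30. But 0.93 is borrowed from prefrail older adults, and the protocol states that no study exists in its own population. The relative loss is larger if the true effect is smaller.

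A reader might infer that the primary p-value and interval are invalid, or that the trial is underpowered. The documents support neither: any error is conservative, the estimate is not biased, and power at the stated effect size meets the planned 80%.

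**Conclusion.** The point holds as one of efficiency. The stratification factor is left out of the default primary test, and the rule that could admit it is tied to the one condition that stratification prevents. The cost runs from nothing (no gender difference in SMM change) to about 12 points of power at an effect of 0.93 and 20 points at 0.60 (a difference of 1.5 SD), with type I error falling to between 1.4 and 2.1% at that extreme. These sizes assume 54 evaluable participants, effects in within-gender SD, and a gender difference that the documents do not supply. Baseline SMM is a minor addition. Because the remedy costs almost nothing even if the gender difference is nil, this is a free improvement and not the correction of an invalid analysis.

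**What to change.** Pre-specify the primary analysis as ANCOVA of week-12 SMM (or change in SMM) on arm, gender as randomised and baseline SMM, and report the adjusted mean difference with its 95% confidence interval. Delete the sentence that makes adjustment depend on significant baseline differences. Use the same model for the continuous secondary outcomes, each with its own baseline value. Keep the two-sample t-test or Mann-Whitney test as a sensitivity analysis.

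The cost is wording and two degrees of freedom. All the data are already collected. If neither covariate predicts the outcome, the loss of power is under one percentage point (90.8% against 90.2% in simulation with 26 per arm at 0.93).

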**Method and analysis:**

A total of 72 Chinese adults with obesity will be randomised to receive HMB-enriched nutritional supplements (65 g/day) or a placebo for 12 weeks. Participants in both groups will also receive calorie restrictions based on the individualised nutrition guidance of dietitians. Participants and investigators will be blinded to the allocations. The primary outcome will be the mean change in whole-body skeletal muscle mass (measured by bioelectrical impedance analysis). The secondary outcomes will include the mean change of appendicular skeletal muscle mass, body fat mass, basal metabolic rate, phase angle, muscle function and serum biomarkers. The enrolment will commence in December 2021 and will proceed until March 2022.

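### The primary outcome is a mean change in skeletal muscle mass, but a normality check on the data may replace the comparison of means with a rank test

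*Protocol article*

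**What the plan says.** The abstract and the Primary outcome section both name a mean: "The primary outcome will be the mean change in whole-body skeletal muscle mass" and "The mean change in whole-body skeletal muscle mass (SMM) from the beginning to the end of the 12-week intervention".

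Under Statistical analysis plan, the rule for testing that outcome is: "The independent two-sample t-test or Mann-Whitney U test will be used based on the distributional normality". The same section applies the primary-outcome methods to the secondary outcomes.

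Three other statements bear on the point:

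- Randomisation is stratified by gender: "Gender is first used as a stratification factor, and 36 cases of each gender will be included".
- Covariates, gender included, enter only on a condition: "We will make adjustments based on the covariates if there are significant demographic differences between the groups or if baseline variables differ significantly".
- The analyst does not know the allocation: "The statistical analysis will be performed by an independent statistical expert blinded to the group allocation".

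**The concern.** The outcome is stated as a mean change, so the matching effect measure is a between-arm difference in mean change, in kg. The rule lets the observed distribution decide whether means are compared at all. If the check fails, the primary test becomes a Mann-Whitney test. That test asks whether values in one arm tend to exceed values in the other. This is the same question as a difference in means only when the two distributions have the same shape and differ by a shift. The test also supplies no estimate in kg.

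What is at stake is the meaning of the primary result. Which quantity was tested would be known only after the outcome data had been looked at, and it could differ from one secondary outcome to the next. The protocol states this rule outright, so it is not a detail left open for a separate analysis plan.

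**Working it through.** The plan gives no figure on this point to reproduce. The check asks how often the rule would switch tests, and what the switch would do.

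**Inputs from the protocol.** There are 72 participants at 1:1, so 36 per arm. Attrition of 25% leaves 36 × (1 − 0.25) = 27 per arm. Alpha is 0.05 two-sided, the effect size in the sample size section is 0.93, and the genders are recruited in equal numbers.

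**Assumptions.** The normality check is Shapiro-Wilk at 5% in each arm, failing if either arm fails. The protocol gives no SMM change or SD by gender, so a range is shown. Rates come from simulations of about 3,000 to 8,000 trials per setting.

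**1. Switching by chance.** With exactly normal data, two independent checks at 5% fail at least once with probability 1 − 0.95² = 0.0975. Simulation gives about 10% at both 27 and 36 per arm.

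**2. Switching because of the gender mix.** All data are normal within gender.

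| Assumed difference between genders in SMM change | Sent to the rank test |
|---|---|
| None | about 10% |
| Mean gap of 1 or 2 within-gender SD, equal SDs | 8–10% |
| Mean gap of 1.0 kg, both SDs 0.8 kg | about 9% |
| No mean gap, SD ratio 1.5 | 16–17% |
| No mean gap, SDs 1.0 and 0.6 kg | about 20% |
| Mean gap of 1.0 kg and SDs 1.0 and 0.6 kg | 32–34% |
| Mean gap of 3 SD, equal SDs | 26% (27 per arm), 40% (36 per arm) |

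A moderate gap in mean loss does not raise the rate above chance. Unequal spread does, and so does a very wide gap.

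**3. Effect on error rates.** With no gender gap in mean, the switching rule has type I error of 0.046 to 0.057, and within each setting it is almost the same as that of the t-test. At an effect of 0.93, the power of the rule and of the t-test differ by at most about 1.5 points. With 27 per arm and no gender difference, power is 0.919 against 0.920. At an effect of 0.5 kg, the two tests run side by side disagree on p<0.05 in about 7 to 9% of trials. The rule uses the rank test only when the check fails, so switching changes the significance call in only 1 to 4%.

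**4. Where the rank test and the mean part company.** These settings have equal true means and equal SDs:

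- Normal shape against exponential shape: Mann-Whitney rejects in 7.8 to 8.4% of trials, and a t-test in 5.1 to 5.6%.
- Opposite skews: Mann-Whitney rejects in 23 to 28%, and a t-test in 6.2 to 6.6%.

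These settings show that the two tests answer different questions. They are not a forecast for this trial.

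**5. The proposed replacement.** A linear model of SMM change on treatment and gender, with no pre-test, has type I error of 0.046 to 0.055 in every setting tried. With 27 per arm and an effect of 0.93 overall SD, its power is 0.917 with no gender gap, 0.96 with a 1-SD gap and 0.997 with a 2-SD gap. The unadjusted t-test gives 0.92, 0.94 and 0.97, and its type I error falls to 0.028 and 0.007 at the 1-SD and 2-SD gaps.

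**The case against.** The strongest reply is that little would change in practice. The protocol gives a rule under which one test applies, and a blinded analyst applies it. Error rates hardly move. If the supplement has no effect at all, the arms share one distribution and both tests are valid. The form of the normality check can be left to a separate analysis plan, and nothing stops the investigators reporting mean changes next to a rank-test p-value. All of this stands, and it limits the point to a mismatch between outcome and test.

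It also rules out three stronger readings that a reader might infer:

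- **That recruiting equal numbers of men and women will itself break normality.** The outcome is a change score, and a gender gap of 1 to 2 SD leaves the failure rate at chance level. Rates of 20% or more need clearly unequal SDs or a gap of about 3 SD, and the protocol supports neither.
- **That the rule inflates type I error.** Excess rejection appears only if treatment alters the shape of the distribution while leaving mean and SD unchanged. Nothing in the protocol suggests that.
- **That the analyst could pick the more favourable p-value.** The blinding statement limits this, and the rule names normality, not the result, as the criterion.

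The reply does not remove the mismatch. Blinding does not fix the quantity tested in advance, and reporting means beside a rank test leaves the formal primary test addressing something else.

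**Conclusion.** The point holds as one of clarity about what the primary analysis estimates. The protocol names a mean change and then states a rule under which the primary test may not compare means. If Shapiro-Wilk at 5% is applied per arm, this would happen in about 10% of trials with perfectly normal data. The share would be about 20 to 40% only under gender differences in spread, or a very wide gap in mean, for which the protocol gives no figure. The effect on type I error and power is negligible, at about 1.5 points or less. The change is worth making because it costs almost nothing and ties the test to the stated outcome. The percentages rest on the assumed normality check and on 27 to 36 per arm. The mismatch itself rests only on the protocol's wording.

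**What to change.** Replace the test-selection sentence with: 'The primary analysis estimates the between-arm difference in mean 12-week SMM change (kg) with 95% CI from one pre-specified linear model with treatment and gender (the stratification factor), whatever a normality check shows; Mann-Whitney is a sensitivity analysis only.'

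Apply the same rule to the continuous secondary outcomes from BIA, grip strength, circumferences and the sit-to-stand test. Reword the conditional-adjustment sentence so that gender is in the model regardless of any baseline test.

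The cost is a sentence of text and that small alignment. No extra participants are needed beyond 72, and the rank test is still reported. The downside is a slight loss of efficiency if the changes prove heavily skewed.
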